## Abstract

**Background:**

Sepsis is still a major health problem that causes high mortality in all populations. Organ dysfunction including sepsis-associated thrombocytopenia is prevalent among sepsis patients, resulting in increasing mortality rates. Considering the clinical role of platelets, thrombocytopenia in sepsis has led to a large spend in research activity and clinical trials in this area, yet there is no consensus upon which treatment should be administered. As a result, platelet transfusion is often indicated to resolve low platelet counts, leading to an increasing risk of the multiple risks transfusion brings, such as infectious or immune system complications. Given the role of thrombopoietin in stimulating proliferation and differentiation of megakaryocytes, our previous study investigated the potential benefits of recombinant human thrombopoietin in severe sepsis patients with thrombocytopenia. However, there are several limitations in the study, which may have led to bias in our conclusion. Thus, we are conducting this study in order to evaluate the safety and efficacy of recombinant human thrombopoietin in a large, varied population.

**Methods/Design:**

The study is designed as a randomized, open-label, placebo-controlled, multi-center study in tertiary academic centers for evaluating the safety and efficacy of recombinant human thrombopoietin over placebo. An established total of 708 patients with sepsis and thrombocytopenia will undergo prospective random assignment to recombinant human thrombopoietin or placebo (a 1:1 ratio). The primary endpoint is 7-day all-cause mortality and 28-day all-cause mortality.

**Discussion:**

To our knowledge, this is the first study to evaluate the safety and efficacy of recombinant human thrombopoietin among severe sepsis patients with thrombocytopenia in a varied population. With our study, the level of evidence for the treatment of these patients will be significantly raised.

**Trial registration:**

ClinicalTrials.gov: NCT02094248. Registration date: 23 March 2014.

**Electronic supplementary material:**

The online version of this article (doi:10.1186/s13063-015-0746-6) contains supplementary material, which is available to authorized users.

## Background

Defined as a systemic deleterious host response to infection, sepsis is still a major healthcare problem around the world [1]. It is characterized by the cardinal signs of inflammation, including vasodilation, increased microvascular permeability and cell dysfunctions [2].

Despite their small size and anucleate status, platelets have diverse roles in vascular biology during sepsis. Not only are platelets the cellular mediator of thrombosis, but platelets are also immune cells that initiate and accelerate many vascular inflammatory conditions [3]. Due to a response to a systemic bacterial infection, continued platelet activation in sepsis patients is prevalent, leading to sepsis-associated thrombocytopenia [4]. Researches have suggested that the declining platelet counts (PCs) are associated with mortalities among sepsis patients caused by various diseases, indicating the importance of recovering from thrombocytopenia during sepsis [5, 6].

To date, evidence-based treatment strategies for sepsis-associated thrombocytopenia have not yet reached consensus for clinical practice. The management of thrombocytopenia remains a challenge. In the guidelines of surviving sepsis, platelet transfusion is advised to be administered when PCs are below 10 × 10^9^/L in the absence of apparent bleeding or below 20 × 10^9^/L if the patient has a significant risk of bleeding [1]. Studies have reported that early recovery from thrombocytopenia helps to prevent coagulopathy and decreases the mortality rate [7, 8]. Taking all of the above into account, more aggressive approaches to reverse the pathophysiological process of thrombocytopenia in severe sepsis are indeed required.

Several growth factors are involved in the process of platelet generation. Among them, thrombopoietin, which has been identified for its ability to stimulate proliferation and differentiation of megakaryocytes, has been identified [9]. Recent study has demonstrated the role of thrombopoietin as an effective stimulus for promoting hematopoietic stem cells when administered before radiotherapy to minimize hematopoietic stem cell injury and mutagenesis in mice, indicating the varied potentials of this factor [10].

Our previous study demonstrated that administration of recombinant human thrombopoietin (rhTPO) with conventional medical therapies could significantly improve the PCs in severe sepsis patients with thrombocytopenia and effectively reduce the platelet transfusion possibility [11]. We also observed significantly different mortality rates between the intervention group and the control group. This previous study is a single-center non-randomized prospective study. There are several limitations in the study, which may have led to bias in our conclusion. Thus, we have designed a clinical study that will evaluate the safety and efficacy of rhTPO in a large, varied population.

## Methods

### Objectives

The objective of this study is to determine the safety profile and efficacy profile of rhTPO in a large, varied severe sepsis population.

### Study design

The study is designed as a randomized, open-label, placebo-controlled, multi-center study in 17 tertiary academic medical centers. The sites that are participating in this study are medical, surgical or emergency ICUs. Patient enrollment is expected to last up to 18 months. The end of the study is defined by the last follow-up of the last enrolled patient. The trial is registered at clinicaltrials.gov (NCT02094248).

Qualified patients will be randomized into either of the two groups: the intervention group and the control group. Both groups receive standard care and will receive appropriate medical support based on guidelines issued by the surviving sepsis campaign [1].

The intervention group will receive administration of rhTPO (TPIAO™, Shenyang Sunshine Pharmaceutical Company Limited (SUNSHINE), Shenyang, China). The rhTPO will be subcutaneously injected in the intervention group after randomization. The dose is 15,000 U per day. The subcutaneous injection will be terminated when PCs are increased by 50 × 10^9^/L for 2 consecutive days compared with PCs at baseline. The duration of rhTPO will be 7 days. Time from randomization to administration of rhTPO will be within 24 hours.

Patients in the control group will receive the equal amount of normal saline, which will be subcutaneously injected as a placebo. The normal amount of saline is 1 ml per day for the initial stage and the maintenance stage. The subcutaneous injection will be terminated after 7 days. Time from randomization to administration of placebo will also be within 24 h.

### Recruitment

A principle investigator, assisted by a well-trained study coordinator in each participating center, will identify potentially eligible patients based on the eligibility criteria. And they, in collaboration with the treating physician, will confirm patient eligibility for the trial. The study coordinator will then obtain written informed consent from the patient. Patients will be consecutively enrolled at each of the participating centers whenever a study coordinator is available for enrollment. Consent will be obtained from participating clinicians before or at the time of patient consent.

### Eligibility and exclusion criteria

The detailed eligibility and exclusion criteria are listed in Additional file 1.

### Eligible, non-randomized patients

Eligible, non-randomized patients will be those who meet all inclusion criteria but are not included in the trial because of refusal of consent or inability to obtain consent within 12 h of the patient meeting the eligibility criteria. For these patients, we will collect data of platelets at baseline and at the time of eligibility, severity of illness at the time of eligibility, and their vital status in the ICU and at hospital discharge. The collection of these data will enable comparisons with randomized patients to assess threats to the generalizability of the trial results.

### Screening

Given the dynamic nature of the inclusion criteria, research coordinators will screen patients in each study center for eligibility once a day, either the morning or afternoon. Research coordinators will discuss all patients who meet the inclusion criteria, without an exclusion criterion, with the attending intensivist to confirm the inclusion.

### Randomization

Patients will be randomized after informed consent is obtained and it is confirmed that all inclusion and no exclusion criteria are met, prior to the patient-clinician discussion of treatment options and patient risk. Allocation will be based on a 1:1 ratio between the intervention and control groups. The allocation sequence will be generated by utilizing the ResMan Research Manager central randomization clinical trial management public platform (http://www.medresman.org/). The randomization will be stratified by study site. On the day of inclusion, investigators will log information into the web database using user identifications and passwords to obtain the randomization numbers and allocated groups for the eligible patients. Both investigators and participants will be aware of the allocations.

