### Blinding

No blinding will take place in this study. Eligible patients who have given consent will be randomized into either of the two groups.

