### Type of analysis

We will utilize an intention-to-treat approach to examine differences in the mortality in the two groups in the primary analysis by the Pearson χ2 test. Safety parameters and secondary efficacy parameters will be analyzed using the Pearson χ2 test and logistic regression (if necessary). Cox proportional hazards models and the Kaplan-Meier method will also be applied. Adverse events will be tabulated according to randomized group assignment and the proportions will be compared using Fisher’s exact test.

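### The Randomization section places the discussion of treatment options and patient risk after allocation, when the arm is already known, and so adds an avoidable opening for arm-dependent refusal or withdrawal

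*Protocol article*

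**What the plan says.** The order of events is set in the Protocol article, Methods.

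- **Recruitment.** Once eligibility has been confirmed with the treating physician, "The study coordinator will then obtain written informed consent from the patient". The section mentions no discussion of options or risk before that step.
- **Randomization.** "Patients will be randomized after informed consent is obtained and it is confirmed that all inclusion and no exclusion criteria are met", and this happens "prior to the patient-clinician discussion of treatment options and patient risk". The section also states "Both investigators and participants will be aware of the allocations".
- **Blinding.** "No blinding will take place in this study".
- **Study design.** "Time from randomization to administration of rhTPO will be within 24 hours". The same limit applies to the saline arm, whose patients receive daily subcutaneous saline for 7 days.
- **Type of analysis.** The test for the mortality comparison is the chi-square test, and the population is set as follows: "We will utilize an intention-to-treat approach to examine differences in the mortality in the two groups in the primary analysis".
- **Data management.** Patients are assessed daily to day 7. Vital status at day 28 comes from chart review, with direct contact if needed.

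The section on ethics committee approval says that a consent form and a participant information sheet were submitted. Their content is not shown.

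**The concern.** The Randomization sentence fixes a sequence: consent, then allocation, then the clinician's discussion with the patient. Because the trial is open-label, both parties to that discussion can know the arm when it takes place. Two things follow.

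First, the document does not show that the clinician's discussion of options and risk comes before the patient agrees to take part. One arm receives saline injections, and a patient would want to weigh that beforehand.

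Second, a discussion of treatment options has no evident role once treatment has been assigned, except to reopen the assignment. If it differs by arm, it can prompt refusal or withdrawal that differs by arm. Refusal of rhTPO would dilute the intention-to-treat contrast. Withdrawal that also ends data collection would leave outcomes missing in a pattern related to the arm.

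Nothing in the design needs the discussion to come after allocation. It is not an intervention, an outcome or a study procedure anywhere in the article.

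**Working it through.** **1. Sequence, section by section.**

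| Step | Source in the Protocol article | Arm known? |
|---|---|---|
| Eligibility confirmed with the treating physician | Recruitment | No |
| Written consent taken by the coordinator | Recruitment; Randomization | No |
| Web randomization, 1:1 | Randomization | Becomes known |
| Discussion of treatment options and patient risk | Randomization (after allocation) | Yes |
| First injection, up to 24 hours after randomization | Study design | Yes |

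The article states only that the discussion follows randomization. Whether it comes before or after the first injection is not fixed. If before, the patient can still refuse every dose with the arm known. No other section gives a different order, so the Randomization sentence stands uncorrected.

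**2. Sample size, to see whether it is touched.** Inputs from Sample size and statistical analysis: control mortality 40%, a 10% difference read as 40% against 30%, two-sided alpha 5%, power 80%. The allocation ratio is 1:1 (Randomization).

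Unpooled formula: n per arm = (0.40 × 0.60 + 0.30 × 0.70) × (1.960 + 0.842)² / 0.10² = 0.45 × 7.85 / 0.01 ≈ 353.2, rounded up to 354. The total is 708, the plan's figure. The pooled formula gives 356 per arm and 712 in total. Power at 354 per arm is 79.8%. Moving the discussion changes none of these inputs, so N is unchanged. The match with 708 also shows that the figure holds no allowance for lost outcomes.

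**3. Illustration of lost outcomes.** The document gives no withdrawal rate, so the rates below are assumptions. The plan's 40% is used for control mortality. Let w be the proportion of the control arm lost and m the mortality among those lost. Observed control mortality = (0.40 − w × m) / (1 − w).

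| w (control only) | Power if lost at random | Observed, m = 20% | Observed, m = 60% | Shift |
|---|---|---|---|---|
| 2% | 79.4% | 40.4% | 39.6% | ±0.4 points |
| 5% | 78.8% | 41.1% | 38.9% | ±1.1 points |
| 10% | 77.7% | 42.2% | 37.8% | ±2.2 points |

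Example at 5%: (0.40 − 0.05 × 0.20) / 0.95 = 0.4105, and (0.40 − 0.05 × 0.60) / 0.95 = 0.3895.

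Outer bounds at 5% (18 of 354 controls; expected deaths 0.40 × 354 = 141.6): if all 18 died, (141.6 − 18) / 336 = 36.8%; if all 18 survived, 141.6 / 336 = 42.1%. These are limits and not expectations.

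**4. What the illustration cannot do.** It applies only if vital status is lost, and stopping injections does not by itself lose it. It also cannot separate withdrawal caused by the timing of the discussion from withdrawal caused by open-label knowledge of the arm. No part of the shift can be assigned to the quoted clause.

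**5. Which outcomes are exposed.** Mortality can be read from the chart for a patient who has stopped injections. Recovery from thrombocytopenia by day 7, time to a normal platelet level, platelets transfused and bleeding depend on continued daily assessment. A patient who withdraws in the first week loses more of that information.

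**The case against.** The strongest case on the other side has four parts.

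- **Consent may be fully informed.** A reader might infer that patients consent uninformed. The document does not support that. The same sentence requires informed consent before randomization, the trial commits to the Declaration of Helsinki, and a consent form and information sheet went to the ethics committee. The coordinator may explain options and risks at consent. This stands: the text leaves the timing of the clinician's discussion unsatisfactory but does not prove that consent is uninformed.
- **The content of the later talk is unknown.** The article does not say what each arm is told, that this is the first or only discussion of risk, or that a choice is offered. Patient risk could mean the patient's own prognosis. This also stands, so the claim is only that the talk can differ by arm.
- **Open-label knowledge would allow withdrawal anyway.** This is correct, and reordering does not remove that knowledge. It removes one additional occasion, a discussion of options held after the arm is known.
- **Mortality is well protected.** Intention-to-treat analysis and chart-review vital status limit bias in the primary outcome. This stands, and it argues against the stronger inference that the mortality comparison is broken.

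One defence does not hold: that a journal article merely condenses a fuller protocol. The article does not omit the order. It states one.

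**Conclusion.** The point holds as a badly fixed sequence, of moderate severity. The Randomization section places the discussion of options and risk after allocation in an unblinded trial. No other section corrects this and nothing in the design requires it. As written, consent is not shown to follow that discussion, and the order adds an avoidable opportunity for arm-dependent refusal or withdrawal.

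The size cannot be computed from the document. Under assumed one-arm losses of 2% to 10%, with mortality of 20% or 60% among those lost, the shift in observed control mortality is about 0.4 to 2.2 points against a 10-point target. That holds only if vital status is lost, and only part of such loss could be due to the order of steps. The day-7 platelet, transfusion and bleeding outcomes are more exposed than mortality. The sample size of 708 reproduces and is unaffected.

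**What to change.** Amend the Randomization sentence to say that the discussion of both treatments and their risks, including the possibility of saline injections, is completed before consent is signed and before the web randomization is called. Add that no discussion of treatment options is reopened on the basis of the allocation.

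No change is needed to the sample size, the intention-to-treat analysis or the collection of day-28 vital status.

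The cost is a one-sentence amendment and retraining at the 17 centres. The trial status section says recruitment is under way, so the change would apply to patients not yet enrolled. A few patients may decline before randomization. They would then fall among the eligible, non-randomized patients whom the article already plans to describe.

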### Blinding

No blinding will take place in this study. Eligible patients who have given consent will be randomized into either of the two groups.

### Study flowchart

The study flowchart is listed in Additional file 2.

## Outcome measurements

### Primary outcome

The primary outcome of this study is the 7-day all-cause mortality and 28-day all-cause mortality.

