## Statistical analysis

### Sample size and statistical analysis

The all-cause mortality of sepsis varies in different patient populations. The mortality of 28-day ranges from 20.8% to 61% but no reliable 7-day mortality has been reported to our knowledge [12, 13]. Using the 28-day mortality in our center, we assumed that the 7-day mortality is 40%. Our sample size was calculated to detect a 10% difference in mortality at day 7 between the two groups with a two-tailed test, a significance level (alpha) of 5% and a power of 80%. We plan to include a total of 708 subjects.

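### Two unranked primary endpoints (7-day and 28-day mortality), but alpha, power and the 708 patients are set for one test at day 7

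*Protocol article*

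**What the plan says.** The *Primary outcome* section reads: "The primary outcome of this study is the 7-day all-cause mortality and 28-day all-cause mortality". The abstract (*Methods/Design*) agrees: "The primary endpoint is 7-day all-cause mortality and 28-day all-cause mortality". Neither place ranks the two time points or says whether one or both must show a difference.

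Under *Sample size and statistical analysis*, the design calculation concerns one of them: "Our sample size was calculated to detect a 10% difference in mortality at day 7 between the two groups". The control rate is an assumption ("we assumed that the 7-day mortality is 40" per cent), and the error rates are given once, as "a significance level (alpha) of 5% and a power of 80" per cent. The result is: "We plan to include a total of 708 subjects". For day 28 the section gives only a published mortality range of 20.8% to 61%, with no design rate, effect or power.

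Under *Type of analysis*, the intention-to-treat comparison is of "differences in the mortality in the two groups in the primary analysis by the Pearson χ2 test". It names no time point and gives no rule for combining two results.

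**The concern.** The outcome section fixes two primary endpoints, while the sample-size section spends all of the alpha and power on one. The stated operating characteristics then describe the trial's decision only under a rule that the article does not state. Two things are at stake:

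- **Error rate or power.** If either endpoint can carry the claim, two tests at 5% give more than 5% overall. If both are needed, joint power cannot exceed the power at day 7 alone, and it is lower whenever the two results can differ.
- **Split results.** One endpoint may be significant and the other not. The article does not say what such a result would mean, and it is not rare even when the drug works as planned (see the check).

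The matter weighs more here because the trial is open-label and already recruiting, so the deciding endpoint should not stay open while outcomes accrue.

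**Working it through.** **Inputs from the article:** day-7 control mortality 40%; a 10% difference; two-sided 5%; power 80%; 1:1 allocation; 708 in total, so 354 per arm.

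**Assumptions made here:** 28-day control mortality of 45% to 61% (the article gives only 20.8–61%), and a 10-point difference at day 28 unless stated otherwise.

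**1. Reproduce 708.** With unpooled variance and 40% against 30%:

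n = (1.960 + 0.842)² × (0.4×0.6 + 0.3×0.7) / 0.10² = 7.849 × 0.45 / 0.01 = 353.2

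This rounds up to 354 per arm, 708 in total, an exact match. The pooled formula gives 712, a continuity correction 752, a one-sided test 562, and 40% against 50% gives 776. So 708 is one day-7 test at an unsplit 5%, with no allowance for a second endpoint.

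**2. Power of each test with 354 per arm.** Power = Φ(x), where x = (d − 1.96·SE₀)/SE₁, SE₀ uses the pooled rate and SE₁ the separate rates.

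- Day 7, 40% v 30%: x = (0.100 − 1.96×0.03585)/0.03565 = 0.834, power 79.8%.
- Day 28, 50% v 40%: x = (0.100 − 1.96×0.03739)/0.03720 = 0.718, power 76.4%.
- Day 28, 61% v 51%: power 76.5%.

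**3. Correlation.** Deaths by day 7 are also deaths by day 28, so the two test statistics have correlation ρ = √[p₇(1−p₂₈) / (p₂₈(1−p₇))]. For 40% and 50%: √(0.20/0.30) = 0.816.

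**4. If either endpoint suffices at 0.05 each.** Type I error = 1 − P(|Z₇| < 1.96 and |Z₂₈| < 1.96), bivariate normal:

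| Day 7 | Day 28 | ρ | Type I error |
|---|---|---|---|
| 40% | 45% | 0.903 | 7.0% |
| 40% | 50% | 0.816 | 7.7% |
| 40% | 55% | 0.739 | 8.2% |
| 40% | 61% | 0.653 | 8.6% |

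The article takes its 40% for day 7 from the centre's 28-day mortality. If 28-day mortality is really 40% and day-7 mortality is 15–30%, the error is 7.8–9.0%. Independent tests would give 1 − 0.95² = 9.75%. If nobody died after day 7, the endpoints would coincide and the error would stay at 5%.

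**5. If both must be significant.** Joint power = Φ₂(x₇, x₂₈; ρ), with ρ averaged over the two arms and day 7 at 40% v 30%:

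| Day 28 | Both significant | At least one | Exactly one (split) |
|---|---|---|---|
| 45% v 35% | 73% | 84% | 11% |
| 50% v 40% | 71% | 86% | 15% |
| 61% v 51% | 68% | 88% | 20% |
| 50% v 43% | 45% | 81% | 35% |

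The split column is the difference between the two columns before it, taken before rounding.

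**6. Simulation check** (400,000 trials, nested deaths, Pearson χ²). Either-endpoint error was 7.5% (40%/50%) and 8.6% (40%/61%). Joint power was 71% (50% v 40% at day 28) and 69% (61% v 51%).

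**7. If alpha were split equally.** At two-sided 0.025, x₇ = (0.100 − 2.241×0.03585)/0.03565 = 0.551, so day-7 power is 70.9%. Keeping 80% would need 864 patients (pooled) or 856 (unpooled).

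**The case against.** The best reply is that this is a journal article. The full protocol or the analysis plan may hold the testing rule, and its absence from an article is not a defect in itself. That is fair, and the point does not rest on it. The article itself names two primaries and sizes the trial for one, and several rules that an unseen plan might contain would not reconcile the two: an equal alpha split leaves about 71% power at day 7, and a both-required rule about 69–71%. Only letting day 7 decide, or testing it first, keeps the stated pair, and the outcome section should then say so.

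Three stronger readings are tempting but not supported:

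- *That each endpoint is to be tested separately by χ².* This is a natural inference, but the analysis section says neither that nor which time point it means.
- *That the trial may claim success on whichever endpoint crosses 0.05.* This follows only if either suffices. The article joins the two with a plain conjunction and never offers them as alternatives. If both are required, the type I error is at most 5% and the loss is in power.
- *That 5% and 80% are wrong on every reading.* They are right together if day 7 alone decides. Under the either-endpoint reading, the chance of at least one success is not below the day-7 power; it is the 5% that fails.

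It is also fair to say that the joint-power figures depend on day-28 inputs that the article does not supply.

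**Conclusion.** The point holds as a mismatch between the primary outcome and the design calculation. The 5% and 80% describe a trial decided by day 7 alone, and the article does not state that rule. The type I error is about 7–9% if either endpoint suffices, which assumes that some deaths occur after day 7. Joint power is about 69–71% if both are required, with day 7 at 40% v 30% and assumed day-28 rates of 50% v 40% or 61% v 51%. It falls to about 45% if the day-28 difference is only 7 points (50% v 43%). The exact figures move with those assumptions. What does not depend on them is that 708 was derived for one day-7 test. The decision rule needs to be fixed because it governs the trial's main mortality claim.

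**What to change.** Before any outcome data are compared by arm, state a fixed-sequence rule in the abstract, *Primary outcome* and *Type of analysis*. Test 7-day all-cause mortality first at two-sided 5%; test 28-day all-cause mortality at two-sided 5% only if day 7 is significant. This holds the overall error at 5%, keeps about 80% power for the first test with 708 patients, gives split results a meaning, and leaves the sample-size paragraph as it is.

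If the sponsor prefers day 28 first, the sample-size paragraph must be restated with a day-28 rate, effect and power. With 708 patients, power is about 76–77% for a 10-point difference from 50% or 61%; 80% would need about 776 or 772 patients (pooled formula).

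Cost: no new data are needed, because vital status at day 28 is already collected. The article's own *Protocol amendments* section requires a formal amendment with ethics approval, and the registry entry should match. The downside is that the endpoint placed second can no longer support a positive claim alone: with day 7 first, a day-28 benefit after a non-significant day-7 result would be exploratory.
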